**Good Clinical Practice (GCP)**

This trial will adhere to the principles outlined in the International Conference on Harmonisation Good Clinical Practice (ICH GCP) guidelines, protocol and all applicable local regulations.

**Audits and Inspections**

The study may be subject to audit by the London School of Hygiene & Tropical Medicine under their remit as sponsor, the Study Coordination Centre and other regulatory bodies to ensure adherence to GCP.

**List of Acronyms**

ACF Action Contre la Faim

cRCT Cluster-randomized Controlled Trial

CIFF Children’s Investment Fund Foundation

ComPAS Combined Protocol for Acute Malnutrition Study

CHW Community Health Worker

CMAM Community-based Management of Acute Malnutrition

CSB Corn-Soy Blend

DMC Data Monitoring Committee

ENN Emergency Nutrition Network

ECHO European Commission Humanitarian Aid Office

GCP..................................................................................................Good Clinical Practice

GNC Global Nutrition Cluster

IYCF Infant and Young Child Feeding

IMCI Integrated Management of Childhood Illness

ICMJE International Committee of Medical Journal Editors

IRC International Rescue Committee

LSHTM London School of Hygiene and Tropical Medicine

MSF Médecins Sans Frontièrs

MUAC Mid Upper Arm Circumference

MoH Ministry of Health

MAM Moderate Acute Malnutrition

MANGO Modelling an Alternative Nutrition Protocol Generalizable to Outpatient Care

NGO Non Governmental Organization

OFDA .USAID Office of U.S. Foreign Disaster Assistance

OTP Outpatient Therapeutic Program

PI Principal Investigator

RUSF Ready to Use Supplementary Food

RUTF Ready to Use Therapeutic Food

REC/IRB Research Ethics Committee/Institutional Review Board

SQUEAC Semi-quantitative Evaluation of Access and Coverage

SFP Supplementary Feeding Program

SAM Severe Acute Malnutrition

UNICEF The United Nations Children’s Emergency Fund

UN The United Nations

UNHCR United Nations High Commissioner for Refugees

USAID................................................United States Agency for International Development

WHZ Weight for Height Z-score

WFP World Food Programme

WHO World Health Organization

# Administrative information

## Title Combined Protocol for Acute Malnutrition Study (ComPAS)

## Trial registration: ISRCTN 30393230

## Protocol version 16 March 2017

## Funding United States Agency for International Development/Office of Disaster Assistance (USAID/OFDA) and the Children’s Investment Fund Foundation (CIFF).

**Indemnity**

London School of Hygiene & Tropical Medicine holds Public Liability ("negligent harm") and Clinical Trial ("non-negligent harm") insurance policies which apply to this trial.

### 5c. Role of study sponsor and funders

The trial funders (OFDA, CIFF) were involved in choice of study sites and part of the consultative committee who were consulted about study design. They will however have no role in the collection, management, analysis, and interpretation of data; writing of the report; and the decision to submit the report for publication.

### 5d. Composition, roles, and responsibilities

The ComPAS study is managed by a **global research team** of members from the International Rescue Committee, ACF USA, and the MoH in South Sudan and Kenya. The IRC is the lead agency for the ComPAS study and the implementing partner with the MoH, UNICEF and WFP in Kenya, with ACF-USA as the implementing partner with the MoH, UNICEF and WFP in South Sudan. The LSHTM is the lead academic partner providing expertise in nutrition, statistics and epidemiology. ACF-UK is the prime holder of the CIFF grant and leader of the SAM 2.0 research consortium, of which ComPAS is a sub-grantee.

ComPAS is guided by an **expert scientific committee** including [name] (LSHTM), [name] (University of Tampere and University of Copenhagen), [name] (Washington University of St. Louis), and [name] (LSHTM), who helped interpret the data in Stage 1 and developed the treatment to be used in this study protocol. The expert scientific committee will make recommendations on any medical or epidemiological question that arises during the study design, implementation and interpretation of results.

ComPAS is also guided by a **global consultative committee** of senior nutritionists from The United Nations Children’s Emergency Fund (UNICEF), World Food Programme (WFP), USAID/OFDA, CIFF and European Commission Humanitarian Aid Office (ECHO). The consultative committee helped review and finalize this study protocol, and will play a key role in supporting the implementation of the study, as well as reviewing the results and proposing next steps at a policy level.

#

# Introduction

## Background and rationale

### 6a. Description of research question and justification for undertaking the trial

#### Description of research questions

IRC and ACF-USA, funded by OFDA and CIFF, supported by the LSHTM and in coordination the Ministries of Health in Kenya and South Sudan and will test a new nutritional protocol for the treatment of acute malnutrition that combines the treatment of Severe Acute Malnutrition (SAM) and Moderate Acute Malnutrition (MAM) to be implemented within the existing Community-based Management of Acute Malnutrition (CMAM) model. The goal of the Combined Protocol for the Treatment of Acute Malnutrition (‘Combined Protocol’) is to simplify and unify the treatment of severe and moderate acute malnutrition into one protocol in order to improve the global coverage, quality, continuity of care, and cost-effectiveness of acute malnutrition treatment.

Stage 1 of ComPAS began in October 2014. The specific objective of Stage 1 was to use observational data to analyze the growth of children recovering from acute malnutrition in OTP’s (Outpatient Therapeutic Program) and SFP’s (Supplementary Feeding Program) in order to assess energy requirements and propose an optimized dose of RUTF correlated with MUAC category. To do this, a statistical analyst examined data from anonymized databases provided by ACF-USA, Médecins Sans Frontières (MSF)-France and IRC, and observed the rate of growth and energy needs of children who ultimately achieved intended recovery goals. The results of the analysis were assessed by the ComPAS global team and the expert task force in London in January 2016 in order to develop this study protocol. The results from Stage 1 are presented at the end of section 6a (ii).

In Stage 2, the ComPAS study will address the following question:

What are the program quality indicators (recovery, defaulter, death, length of stay, average daily weight and Mid Upper Arm Circumference (MUAC) gain), and coverage following treatment under the Combined Protocol compared to the standard treatment of OTP and SFP?

#### Justification and summary of relevant studies

Prevalence surveys suggest that acute malnutrition affects approximately 7.5% of the world’s children under 5 years of age, with approximately 34 million children affected by MAM and 16 million children affected by SAM [^[[1]](#endnote-1)^]. Acute malnutrition is a continuum condition, but SAM and MAM are treated separately, with different protocols and therapeutic products managed by separate United Nations agencies. Although children with MAM are three times more likely to die than well-nourished children [^[[2]](#endnote-2)^], many nutrition programs offer treatment only of SAM due to resource and logistical constraints and the challenges of coordinating two separate programs.

There is global consensus around the use of Ready to Use Therapeutic Food (RUTF) for the treatment of SAM, but the treatment of MAM still lacks globally-accepted guidance. There have been many studies testing the efficacy or effectiveness of different products and supplements for the treatment of MAM, but the focus in MAM research has remained largely product-based with MAM regarded as a separate condition from SAM. The addition of milk protein to Ready to Use Supplementary Food (RUSF) appears to improve long-term outcome. A paper by Chang et al (2013) evaluating different products for the treatment of MAM demonstrated that sustained recovery was significantly more likely in those treated with soy + whey (RUSF) compared to either soy RUSF or corn-soy blend (CSB)++[^[[3]](#endnote-3)^]. During a 12-month follow-up period, only 63% of cured children remained well-nourished, 17% relapsed to MAM, 10% developed SAM, 4% died and 7% were lost to follow-up. Children treated with soy/whey RUSF were more likely to remain well-nourished (67%) than those treated with CSB++ (62%) or soy RUSF (59%) (P=0.01). RUTF for the treatment of children with SAM includes milk protein. Treating MAM with RUTF would provide MAM children with a high quality nutritional supplement, while reducing the logistics and cost of procuring a second product and managing a separate program for supplementary feeding.

The current protocol for SAM bases RUTF dosage on weight (175-200 kcal/kg/day) until children are discharged as cured, but children may not require as much energy towards the end of treatment. Ashworth (1969) demonstrates that in an inpatient setting, as children reach the discharge criteria, their food intake drops 30%, reflecting the concept that as children progress through treatment, their rate of growth slows and their supplemental energy needs decrease. One hypothesis suggests the composition of the tissue developed as children approach and then exceed discharge criteria changes from primarily lean muscle mass to fat mass, though more evidence is needed [^[[4]](#endnote-4)^]. Research from a MSF therapeutic feeding program in Burkina Faso indicates that average weight gain mirrors average MUAC gain and rate of growth using these two metrics slows as children progress through treatment, resulting in a growth ‘plateau’ where treatment gains stagnate [^[[5]](#endnote-5)^]. ACF-France in Myanmar successfully reduced dosage of RUTF to one sachet per day at the end of SAM treatment with similar programmatic results (cured/death/defaulter) as standard dosage of RUTF based on body weight [^[[6]](#endnote-6)^]. ACF is exploring a reduced dosage in SAM treatment through its ‘Modelling an Alternative Nutrition Protocol Generalizable to Outpatient’ (MANGO) research study in Burkina Faso in 2016-2017 [^[[7]](#endnote-7)^]_._

The use of MUAC as the sole anthropometric criteria for screening, admission and discharge has been shown to target those children most at risk for mortality. Rather than using WHZ as an additional criterion, greater sensitivity for the same specificity level for mortality can be achieved by increasing the MUAC cut-off [^[[8]](#endnote-8)^]. Data indicates that raising the MUAC cut-off to 125mm covers all children at risk of acute malnutrition-related deaths [^[[9]](#endnote-9)^]. MUAC-only programming is logistically easier to implement and more effective at detecting high risk children [^[[10]](#endnote-10)^] *.*

In 2013, Washington University initiated a clinical trial in Sierra Leone to test the efficacy of an integrated, MUAC-only based protocol for the treatment of SAM and MAM using one product (RUTF) at different doses for children <115mm (175 kcal/kg/day) and 115-<125mm (75 kcal/kg/day), against the standard protocol of OTP with RUTF for children admitted as SAM and SFP with CSB++ for children admitted as MAM. Children were discharged at a MUAC of 125mm with a package of preventive health care and Infant and Young Child Feeding (IYCF) support. Results from the trial indicate the integrated program had a reduced caseload of SAM, due to earlier treatment of children presenting as MAM, with a comparable recovery rate (83% vs. 79%) and higher coverage (71% vs. 55%, p=0.0005). Children who received integrated management recovered more rapidly, with greater MUAC gain and higher weight for height z- score (WHZ) upon discharge. The cost of RUTF used to treat a SAM case in the integrated program was $36, compared to $68 in the standard program [^[[11]](#endnote-11)^].

Building on the above mentioned studies, Stage 1 of ComPAS retrospectively analysed treatment data from 8,000 acutely malnourished children in five countries (Kenya, South Sudan, Chad, Yemen, and Pakistan) to assess growth trends and energy requirements.

Key findings from Stage 1 of ComPAS include the following:

- Growth trends in MUAC mirror those of proportional weight gain when examined by MUAC at last visit.
- Rates of weight and MUAC gain slow with increasing MUAC.
- Children with higher MUAC measurements need less energy per kilogram body weight to achieve the growth observed than those at lower MUAC measurements.
- When assessed over the range 115mm ≤ MUAC < 125mm, children treated in OTP facilities experienced more growth (defined by weight and MUAC gain) than children treated in SFP facilities
- When assessed by continent, children in Africa (Kenya, South Sudan and Chad) tended to gain weight and MUAC at a higher rate than children in Asia (Pakistan and Yemen). Rates of weight and MUAC gain slow at lower MUAC’s in children in Asia.
- When assessed by each stunting status (<-2 z-scores and ≥-2 z-scores) and age group (<2 years vs ≥ 2 years) at admission, no significant differences in weight and MUAC gain were detected between groups
- 1000 kilocalories a day meets the aim of covering the total energy needs of 95% of children when they have MUAC<115mm, and 500 kilocalories a day meets the aim of covering half the energy needs for 95% of children when they have 115mm ≤ MUAC < 125mm.

Our findings concluded that two 92g sachets of RUTF (1000 kcal) meets the total energy requirements for >95% of children with a MUAC<115mm, and one 92g sachet of RUTF (500 kcal) meets half the energy requirements for >95% of children with a MUAC of 115-<125mm, and serves to simplify and streamline the treatment provided in a combined protocol.

The Stage 1 report of ComPAS is included in annex.

### 6b. Explanation for choice of comparators

The Combined Protocol will be compared against the Standard Protocol (the national protocol in each country). The standard protocol includes treatment of SAM in an outpatient therapeutic program using RUTF (200 kcal/kg/day) and MAM in a supplementary feeding program using RUSF (500 kcal/day), as approved by WHO, UNICEF, WFP, and the Ministries of Health in each country. Both the Combined Protocol and the Standard Protocols for each country are described in detail in section 11.

## Objectives

Primary objective: Determine the impact of the Combined Protocol on recovery compared to the standard treatment of OTP and SFP (recovery defined as achieving ≥125mm MUAC).

Secondary objectives: Determine the impact of the Combined Protocol on coverage, defaulting, length of stay, death rate, average daily weight gain and average daily MUAC gain compared to the standard treatment of OTP and SFP.

Hypothesis: The treatment of acute malnutrition using the Combined Protocol will be as effective as the standard protocol at recovering children from malnutrition as indicated by program exit status, length of stay, and average weekly weight and MUAC gain. Coverage of SAM and MAM treatment will increase under a Combined Protocol by improving early detection of MAM and preventing deterioration into SAM, and by improving program coherence and reducing loss during the transition from OTP to SFP.

## Trial design

The study will be a prospective, multi-center cluster-randomized controlled (cRCT) non-inferiority trial. The unit of randomization will be health facilities stratified by country and then randomly assigned to the control or intervention group. Children in the control group will receive the standard protocol while those in the intervention group will receive the combined protocol.

The study will include a total of 24 clusters in the following categories:

Kenya

| Arm 1 | Control (6) | Standard protocol |
| --- | --- | --- |
| Arm 2 | Intervention (6) | Combined protocol |

South Sudan

| Arm 1 | Control (6) | Standard protocol |
| --- | --- | --- |
| Arm 2 | Intervention (6) | Combined protocol |

# Methods: Participants, interventions, and outcomes

## Study setting

**Description of study settings**

There will be two sites in this multi-center cluster randomized trial: Aweil East County, South Sudan and Nairobi county, Kenya.

Aweil East, South Sudan

Aweil East is a rural setting in Northern Bahr el Ghazal State which contains seven payams, a total population of 538,765 and an under five population of 102,365. It has a total of 13 government health facilities and outreach clinics in the area, all of which are supported by ACF-USA. Each health facility is approximately 20-30 km apart. 12 out of the 13 health facilities will be included in the study.

Nairobi, Kenya

Nairobi county is an urban area with 93 facilities offering treatment for malnutrition, a total population of approximately 3.4 million and an under five population of 450,000. Each treatment facility is approximately 3-5 km apart. 12 health facilities serving primarily internally displaced persons in 3 sub-counties of Nairobi will be selected.

## Eligibility criteria

Table 1: Study Inclusion and Exclusion Criteria

|  | **Inclusion** | **Exclusion** |
| --- | --- | --- |
|  | <125mm MUAC  *and/or*  Bilateral pitting oedema (+)  *and*  Passes appetite test (consumption of 30g of RUTF within 20 minutes)  *and*  No medical complications | ≥125mm MUAC  *or*  Failed appetite test (requires inpatient treatment)  *or*  Medical complications requiring inpatient treatment, as per international guidelines/ IMCI danger signs including but not limited to:   - Oedema (++ or higher) - Anorexia, no appetite - Intractable vomiting - Convulsions - Lethargy, not alert - Unconsciousness - Hypoglycaemia - High fever - Hypothermia - Severe dehydration - Lower respiratory tract infection - Severe anaemia - Skin lesions   *Note:*  For children with WHZ <-2 but a MUAC ≥125mm and no oedema:   - These children will be treated per the protocol provided at the health facility they present to. Their data will not be included in the primary analysis but reviewed in a secondary analysis. - For children presenting at a health facility allocated to the Combined Protocol:   - Children WHZ <-3 will receive two 92g sachets of RUTF/day. All medical aspects of treatment will be the same as the <115mm group.   - Children WHZ ≥-3 but WHZ <-2 will receive one 92g sachet of RUTF/day. All medical aspects of treatment will be the same as the 115mm-<125mm group. - For children presenting at a health facility allocated to the Standard Protocol:   - Treatment will be provided per the national protocol, which is inclusive of children with WHZ <-2.   Data will be collected on the total number of children screened, how many were included/excluded, and the reasons for exclusion from the study. |

Only health facilities that are registered MoH-run facility or mobile nutrition clinic sites will be included in the study. All staff will need to be official ACF, IRC or MoH staff trained in CMAM and the ComPAS study protocol.

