## Interventions

### 11a. Interventions for each group

Table 2: Combined Protocol Intervention: Kenya and South Sudan

| **Combined Protocol** |  |
| --- | --- |
| **Admission Criteria** | <125mm MUAC  AND/OR bipedal oedema (+)  AND clinically uncomplicated (i.e. passes appetite test, no Integrated Management of Childhood Illness (IMCI) danger signs/ no serious medical complications) |
| **Treatment Frequency** | <115mm: Weekly  115-<125mm: Bi-weekly |
| **Dosage** | <115mm and/or oedema (+): Two 92g sachets RUTF/day (1000 kcal/day)  115-<125mm : One 92g sachet RUTF/day (500 kcal/day) |
| **Transition from 2 RUTF to 1 RUTF:** | Two consecutive weekly measurements at or above 115mm and no oedema |
| **Cured** | ≥125mm for 2 consecutive measurements and no oedema, with 3 week minimum stay |
| **Default** | Absent for 3 consecutive visits |
| **Non-recovered** | Has not achieved discharge criteria within 16 weeks |
| **Discharge procedures** | Discharge ration of 7 RUTF sachets |
| **Routine medical treatments (as per national protocol):** | For all children with MUAC <115mm and/or bipedal oedema (+) on admission:   - **Amoxicillin:** Give first dose at health facility and then give remainder to caretaker with instructions to give twice daily for 7 days   For all children with MUAC <125mm and/or bipedal oedema (+) on admission:   - **Malaria**: according to national protocol - **Measles:** one vaccine on 4^th^ visit (4^th^ week) (children >6 months) (unless already vaccinated) - **Deworming:** one dose (albendazole or mebendazole) on the second visit (second week) (children >1 year) |
| **Referral Procedures (as per national protocol)** | Any child who develops medical complications and/or is not responding to treatment will be referred for a medical evaluation and/or to the Stabilization Center.  ‘Not responding to treatment’ will be defined in the following way:   - Failure to gain any weight (non-oedematous children) - Failure to start to lose oedema - Oedema still present - Weight loss since admission to program (non-oedematous children) - Failure of appetite test - Weight loss of 5% of body weight - Weight loss for two successive visits |

Table 3- Standard Protocol Intervention- Kenya

| **Standard Protocol- Kenya** | **OTP** | **SFP** |
| --- | --- | --- |
| **Admission Criteria** | - WHZ < -3   And/or   - MUAC < 115mm   And/or   - Bilateral pitting oedema (+/++) | - Discharged from OTP   And/or   - WHZ <-2 to WHZ >-3  and/or - MUAC 115mm < 125mm |

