## Consent or assent

As this is a cluster randomized trial, consent will be obtained at the health facility level from local health authorities as well as from individual participants.

Health facility-level consent will be discussed between the research coordinator, community leaders and the MoH in each county. Community leaders and local health authorities designated by the MoH will receive a ‘health facility information sheet,’ and will be asked for their consent after they have had an opportunity to review the information and discuss any questions with the research coordinator.

When a caretaker arrives to any health facility included in the ComPAS trial seeking treatment for their malnourished child (either with a referral slip or not), they will first be seen by a community health worker to confirm that they are eligible to receive treatment (i.e., they have a MUAC <125mm, and/or a WHZ <-2 z-scores, and/or oedema). Once their eligibility for treatment is confirmed, they will be seen by the health worker responsible for their care. The health worker will describe the aims of the study as detailed in the ‘participant information sheet,’ ensuring that the caretaker feels comfortable and understands the information. They will be informed that a study is taking place at this health facility and will be given information about what their participation would entail, including how their information will be used, but that they are not obligated to participate. The participant information sheet provides details of the treatments provided in the study. Treatment will be available for all malnourished children who meet the national standards (per the eligibility criteria described above and in the interventions section of the study protocol) regardless of whether they choose to participate in the study or not. If a caretaker has chosen not to participate in the study, they will be assured that their child can still receive the treatment offered by that health facility, and that their information will not be included in the analysis.

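### The Combined arm's rules for oedema and WHZ in Tables 1 and 2 do not agree, which leaves a visit interval, an eligibility rule and re-entry after cure unsettled

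*Protocol*

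**What the plan says.** Two places in the Protocol set the care of a child in a Combined facility: Table 1 in section 10 and Table 2 in section 11a.

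- **Ration, Table 2.** The two lines are "<115mm and/or oedema (+): Two 92g sachets RUTF/day (1000 kcal/day" and "115-<125mm : One 92g sachet RUTF/day (500 kcal/day". Neither mentions WHZ.
- **Visits, Table 2.** Frequency is set by MUAC alone: weekly below 115mm, and "115-<125mm: Bi-weekly". There is no line for oedema or for MUAC ≥125mm.
- **Step-down from two sachets to one, Table 2.** The condition is "Two consecutive weekly measurements at or above 115mm and no oedema".
- **Cured, Table 2.** The condition is "≥125mm for 2 consecutive measurements and no oedema, with 3 week minimum stay", with no WHZ term.
- **Amoxicillin, Table 2.** It is listed for MUAC <115mm and/or oedema (+) on admission. The row heading says that routine treatment follows the national protocol.
- **Eligibility, Table 1.** Inclusion is by MUAC <125mm and/or oedema (+). MUAC ≥125mm is also an exclusion criterion in its own right.
- **WHZ note, Table 1.** It is headed "For children with WHZ <-2 but a MUAC ≥125mm and no oedema". For Combined facilities it states: "Children WHZ <-3 will receive two 92g sachets of RUTF/day. All medical aspects of treatment will be the same as the <115mm group". These children are outside the primary analysis and are kept for a secondary one.

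Section 24 confirms eligibility for treatment if "they have a MUAC <125mm, and/or a WHZ <-2 z-scores, and/or oedema".

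**The concern.** These rows define the intervention under test. Weight and height are measured at every facility (section 15) and oedema is assessed, so staff will recognise the children concerned.

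Three things are at stake. First, where rows conflict for an oedematous child, facilities in the same arm can settle the visit interval or the eligibility question differently. Eligibility also decides who enters the primary analysis. Second, WHZ <-3 counts as severe above 125mm and is ignored just below it. The 115-<125mm children are in the primary analysis, and a reader of the results would need to know whether the difference was intended. Third, a child can be recorded as recovered and at the same moment meet the note's rule for further RUTF. Analysis cannot repair contradictory treatment rows afterwards.

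**Working it through.** The protocol states no figure to reproduce. The check applies the Table 1 and Table 2 rules as written to example children in the Combined arm. WHZ does not alter any oedema row.

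| Child | Table 1 status | Sachets/day | Amoxicillin | Visits |
|---|---|---|---|---|
| 110mm, no oedema, WHZ -3.5 | included | 2 | listed | weekly |
| 120mm, no oedema, WHZ -3.5 | included | 1 | not listed | bi-weekly |
| 130mm, no oedema, WHZ -3.5 | outside primary analysis; note applies | 2 | through the note | not stated |
| 110mm, oedema (+) | included | 2 | listed | weekly |
| 120mm, oedema (+) | included | 2 by the and/or line, though the 115-<125mm line also matches | listed | bi-weekly |
| 130mm, oedema (+) | included and excluded | 2 | listed | not stated |

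**Oedema at 115-<125mm.** The and/or wording of the Dosage row favours two sachets, and the amoxicillin row settles the antibiotic. The only matching frequency line is bi-weekly. If that means every 14 days, as Tables 3 and 4 state for SFP, successive readings are 14 days apart and never form the weekly pair that step-down requires. The dosage, frequency and transition rows cannot all be followed. The interval also matters for outcomes: the two consecutive readings that define recovery are 7 days apart on one schedule and 14 on the other, which feeds into length of stay.

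**Oedema at ≥125mm.** Table 1 inclusion and Table 2 admission both accept this child through and/or, while the stand-alone MUAC exclusion rejects the child. The WHZ note does not help, because it is limited to children without oedema. Table 2 gives a ration but no visit interval.

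**WHZ <-3 without oedema.** At 120mm the ration is 1 × 500 = 500 kcal/day; at 130mm it is 2 × 500 = 1000 kcal/day, with the medical care of the <115mm group. The two rules do not overlap, so each child has one ration. Amoxicillin is less clear at 120mm. The row's list omits the child, but its heading defers to the national protocol, whose OTP (Tables 3 and 4) admits on WHZ <-3 and gives amoxicillin. The same child also meets the SFP MUAC criterion in those tables, so the heading does not settle the matter either way.

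**Re-entry after cure.** Take a Combined child admitted at 120mm with WHZ <-3, who later has two readings ≥125mm, no oedema and at least 3 weeks' stay. Table 2 makes the child cured. If WHZ is still <-3, the child now fits the note (MUAC ≥125mm, no oedema) and the section 24 rule for treatment, at two sachets rather than one. Table 6 in section 12 covers the parallel case in control: those children count as cured on MUAC even if treatment continues until WHZ exceeds -2. There is no matching sentence for the Combined arm.

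**The case against.** The strongest reply is that dosing by MUAC is the intervention. Section 6a argues for MUAC as the sole anthropometric criterion and derives the two ration bands from Stage 1 energy needs by MUAC. On that view Table 2 is right to ignore WHZ, and the note merely provides for children outside the MUAC definition, who are kept out of the primary analysis. The note and Table 2 cover separate groups, so nobody has to choose between two rations on WHZ grounds. Recovery is defined by MUAC and oedema in both arms, and Table 6 shows that the authors foresaw treatment continuing for low WHZ after MUAC cure. Trained research officers, patient cards and weekly data review (sections 18a and 19) mean that what each child received should be on record.

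Much of this stands. A reader might infer that sites will give the same WHZ <-3 child different rations; the documents do not support that, since each such child has one ration rule. A reader might also infer a weekly versus bi-weekly contrast at the 125mm boundary, but the note states no interval. Nor do the documents show that the ration runs in the wrong direction, which is a clinical judgement. The definition of recovery itself is not ambiguous.

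The reply does not reach the oedema rows, which conflict in their own terms. The MUAC-only rationale explains Table 2 but not why the note brings WHZ back as a severity criterion only from 125mm. Good records show what was done; they do not make the instruction consistent. Table 6 covers the control arm only.

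**Conclusion.** The point holds as an internal inconsistency in how the Combined arm classifies severity, in three parts of differing strength.

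- **Oedema:** a direct conflict. At 115-<125mm the frequency and transition rows cannot both be met, taking bi-weekly as every 14 days. At ≥125mm the child is both included and excluded, with no visit interval.
- **WHZ:** two rules that classify severity differently on either side of 125mm, with a two-fold difference in ration (500 v 1000 kcal/day) and no stated reason. The amoxicillin heading leaves some room for interpretation.
- **Re-entry after cure:** addressed for control and not for the Combined arm.

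The consequence is that care can differ for oedematous children and after MUAC cure, not that it will. The documents do not give the share of children with oedema, or with WHZ <-3 at 115-<125mm. For scale only, the recruitment target is 12 × 150 = 1,800 Combined children, so each 1% is 18 children. A reader might assume a share of 5-15% and quote 90-270 children (1,800 × 0.05 and × 0.15). The documents do not support that figure, and it would pool WHZ <-3 children, whose ration is settled, with oedematous children, whose visit interval is not. The finding does not depend on it.

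**What to change.** Amend Tables 1 and 2 so that the inclusion and exclusion criteria, the WHZ note, and the admission, frequency, dosage, transition, medical-treatment and cured rows all use one stated classification. In particular:

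- state whether oedema (+) at MUAC ≥125mm is included, and give every oedema row a visit interval compatible with the transition rule;
- state how WHZ counts at 115-<125mm and at ≥125mm, with the reason if the two differ, and whether the amoxicillin list or the reference to the national protocol governs;
- add a sentence for the Combined arm, parallel to the one in Table 6 for control, on children who meet the MUAC cured rule while still meeting the WHZ note;
- flag in the dataset any re-entry under the note after MUAC cure.

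Which ration, interval or antibiotic rule applies is for the investigators to decide, with their expert scientific committee. The cost is a short amendment to two tables, one added sentence, an ethics notification, a line in research officer training and one data field. No new measurement is needed, because weight, height and oedema are already assessed.
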